### Outcome

2.3

The major result is rate of PU healing or ulcer epithelialization tissue. The secondary result is the changes in the area of ulcer in cm and cost-effectiveness.

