## Methods

2

This study will be implemented from February 2021 to February 2022 at Hangzhou Geriatric Hospital. The experiment was granted through the Research Ethics Committee of Hangzhou Geriatric Hospital (C5259033) and recorded in research registry (researchregistry6294). Sequence of random numbers is generated by a computer. Sequentially numbered sealed opaque envelopes are used for the concealment of random numbers. All the patients taking part in our experiment are randomly divided to polyurethane foam dressing or hydrocolloid dressing group, and each group includes 48 participants.

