### Inclusion and exclusion criteria

2.1

Criteria for inclusion: patients older than 18 years of age who have been diagnosed with PU. If the patient suffers from more than a PU, only the ulcer with largest diameter is evaluated. Criteria for exclusion:

(1)hypersensitivity or allergy to the substances in dressings;(2)patients with diabetic foot or venous ulcers; and(3)serious disease.

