### Statistical analysis

2.4

The analysis of all the data are conducted with the software of IBM SPSS Statistics for Windows, version 20 (IBM Corp., Armonk, NY). The data obtained are represented through the proper features, for example,. standard deviation, and mean, median as well as percentage. And independent *t* tests and χ2-tests are respectively utilized to analyze the categorical variable and continuous variable. When *P* is less than .05, the efficacy is viewed to be statistically significant.

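### Raw change in ulcer area is compared without adjusting for baseline area, so the comparison loses precision and is exposed to chance imbalance in entry size; the unit is also printed as a length

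*Protocol article*

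**What the plan says.** The Outcome section of the protocol article (2.3) defines the outcome in one sentence: "The secondary result is the changes in the area of ulcer in cm and cost-effectiveness". The abstract gives the same unit.

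The Statistical analysis section (2.4) gives the method: "independent *t* tests and χ2-tests are respectively utilized to analyze the categorical variable and continuous variable". As printed, the two tests are attached to the wrong variable types. Read charitably, change in area gets an independent t test. No covariate is named. The threshold is a P value that "is less than .05, the efficacy is viewed to be statistically significant".

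On who enters, the Inclusion and exclusion criteria (2.1) admit "patients older than 18 years of age who have been diagnosed with PU", with no limit on ulcer size or stage. Where a patient has several ulcers, "only the ulcer with largest diameter is evaluated". The Methods section says "Sequence of random numbers is generated by a computer" and "each group includes 48 participants". It mentions no stratification by ulcer size. Table 1 reserves one row, with a P value, for the change in area.

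**The concern.** There are two problems, of unequal weight.

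The lesser one is the unit. A centimetre measures length and an area needs cm². This is clerical. The outcome is named as an area, and diameter is used only to choose which ulcer is followed. The unit still matters in one respect: an absolute unit, whether cm or cm², points to a raw difference and not to a percentage.

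The greater one is the comparison itself. Write change as final area minus baseline area. For every healed ulcer the final area is zero and the change is exactly minus the baseline area. A healed 30 cm² ulcer then scores ten times a healed 3 cm² ulcer, although both patients had the same result. Healing is the primary outcome, so such patients are expected. With no size limit at entry, part of the variance of raw change is variance in entry size, which has nothing to do with the dressing. An unadjusted t test leaves that variance in its standard error and lets any chance difference in entry size pass into the estimate. At stake is a dressing effect on area that is missed, or a difference that owes something to which arm drew the larger ulcers.

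**Working it through.** **Inputs from the document.** 48 per group; significance level 0.05 (taken as two-sided, since sidedness is not stated). No power, target difference, SD of area, correlation or healing rate is given, so there is no sample-size calculation to reproduce. Everything below that needs such a figure is an assumption, shown as a range.

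**Step 1. Difference detectable by the adjusted analysis.** In units of its residual SD, at 80% power:

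d = (1.960 + 0.842) × √(2/48) = 2.802 × 0.2041 = 0.572.

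**Step 2. Power of the unadjusted test for the same true difference.** Let R² be the share of the variance in change that baseline area explains. Leaving baseline out inflates the SD by 1/√(1 − R²), so

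power = Φ(2.802 × √(1 − R²) − 1.960).

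| R² (assumed) | 2.802 × √(1 − R²) | Power, unadjusted | Per-arm n at which the adjusted analysis matches 48 unadjusted: 48 × (1 − R²) |
|---|---|---|---|
| 0.10 | 2.658 | 76% | about 43 to 44 |
| 0.25 | 2.426 | 68% | 36 |
| 0.50 | 1.981 | 51% | 24 |
| 0.75 | 1.401 | 29% | 12 |

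**Step 3. What these R² values correspond to.** Let k be the ratio of the final SD to the baseline SD, and ρ the correlation between the two areas. Then

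1 − R² = k²(1 − ρ²) / (1 + k² − 2ρk).

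With ρ = 0.5:
- k = 1 gives 0.75/1 = 0.75, so R² = 0.25.
- k = 0.5 gives 0.1875/0.75 = 0.25, so R² = 0.75.

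**Step 4. Simulation check.** 4,000 trials of 48 + 48 per scenario, with log-normal baseline area, mean proportional reduction 30%, 40% or 60% (SD 0.30, 0.25 or 0.20, reduction capped at complete healing), and a group effect of 0.6 SD on the proportional scale. Both analyses use the same absolute scale:

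| Coefficient of variation (CV) of baseline area (assumed) | Share of variance explained by baseline | Power, raw-change t test | Power, change adjusted for baseline area |
|---|---|---|---|
| 0.3 | 10–43% | 50–75% | 78–80% |
| 0.5 | 21–65% | 30–62% | 73–75% |
| 1.0 | 36–82% | 13–37% | 58–59% |
| 1.5 | 45–87% | 8–25% | 45–46% |

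The smallest gap is 5 percentage points (75.1% against 80.1%). The largest is 45 (13.0% against 58.3%).

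**Step 5. Type I error.** With no effect (2,000 trials per scenario), the raw-change test rejected in 3.2% to 6.4% of trials, close to the nominal 5%.

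**Step 6. Chance imbalance.** The SE of the difference in mean baseline area, as a share of the mean, is CV × √(2/48): about 10%, 20% and 31% at CV 0.5, 1.0 and 1.5. Under no effect, when the arms happen to differ at baseline by z standard errors, the unadjusted statistic is approximately normal with mean z√R² and variance 1 − R². At R² = 0.50 and z = 2, it rejects with probability of about 1 − Φ((1.960 − 1.414)/0.707) = 1 − Φ(0.77) = 22%. At z = 0 it rejects with probability 2 × (1 − Φ(1.960/0.707)) = 0.6%. Averaged over all randomisations the rate is 5%.

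**The case against.** The strongest defence is that an unadjusted comparison of change is valid under randomisation, the outcome is secondary, and covariate adjustment is often left to a fuller plan. The first two points stand and set the weight of this one: it concerns efficiency. The third stands only in part. The article does not leave the method open. It names one, and that method has no covariate.

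It can also be said that raw change is inferred. The text speaks only of changes in area, and Table 1 gives no unit. That is fair. The absolute unit makes a raw difference the natural reading, but the document should say so. A superscript may have been lost from the unit, which is a further reason to treat the unit as clerical.

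Three stronger readings are tempting, and the document supports none of them.

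- **Change mostly measures entry size, or most of the power is lost.** With no SD, correlation or healing rate in the document, this cannot be stated as fact. On the assumed inputs the loss runs from about 5 percentage points to most of the power, and the large losses need wide baseline spread or a close tie between baseline and change. Having no size limit makes wide spread plausible but does not document it.
- **The test has an inflated false-positive rate.** High rejection rates appear only when one looks at trials selected for imbalance. Lower rates in balanced trials offset them.
- **Percent change shows the full loss.** Percent change does better still in the simulations, but it answers a different question, so the gap to it is not a like-for-like loss of power.

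**Conclusion.** The point holds as a matter of precision for a secondary outcome. Change in ulcer area is stated in an absolute unit, compared without baseline area, in patients whose ulcers may be of any size. Overall type I error stays near 5% and the estimate is not systematically biased. Against an adjusted analysis with 80% power at 48 per arm, the unadjusted test has about 68%, 51% or 29% power when baseline explains 25%, 50% or 75% of the variance in change. These three figures rest on assumed shares of variance, a two-sided 5% level and a normal approximation, and nothing in the document selects among them. The wrong unit is a separate clerical correction. The change is worth making because it costs almost nothing.

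**What to change.** 1. Print the unit as cm² and state that the change is absolute.
2. Make the main analysis of this outcome a linear model of final area on treatment and baseline area. Modelling change instead gives the same treatment coefficient, because it only shifts the coefficient of baseline by one. Report the adjusted difference with its 95% CI.
3. Use robust or bootstrap standard errors, because areas are likely to be skewed and healed ulcers put a cluster of zeros in the final area.
4. Keep the unadjusted t test, and percent change adjusted for log baseline area, as supportive analyses only.
5. When rewording the Statistical analysis section, put the two tests back with their proper variable types.

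The cost is a few sentences and one regression. Baseline area is already needed to compute the change, so nothing new has to be collected.

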### Statistical analysis

2.4

The analysis of all the data are conducted with the software of IBM SPSS Statistics for Windows, version 20 (IBM Corp., Armonk, NY). The data obtained are represented through the proper features, for example,. standard deviation, and mean, median as well as percentage. And independent *t* tests and χ2-tests are respectively utilized to analyze the categorical variable and continuous variable. When *P* is less than .05, the efficacy is viewed to be statistically significant.

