## Result

3

Table 1 will show the comparison of clinical outcomes between 2 groups.

**Table 1 T1:** Comparison of clinical outcomes between 2 groups.

	Polyurethane foam dressing group (n = 48)	Hydrocolloid dressing group (n = 48)	*P* value
Rate of pressure ulcer healing			
Changes in the area of ulcer			
Medical cost			
Frequency of dressing			
Length of hospitalization			
Complications			

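### The statistical analysis section assigns t tests to categorical variables and chi-square tests to continuous ones; followed literally, this loses most or all of the power for the numeric outcomes in Table 1.

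*Protocol article*

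**What the plan says.** Section 2.4 (Statistical analysis) of the protocol article pairs tests with variable types in one sentence: "independent *t* tests and χ2-tests are respectively utilized to analyze the categorical variable and continuous variable". It then sets the threshold: "When *P* is less than .05, the efficacy is viewed to be statistically significant". The article gives no other rule for choosing a test.

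The outcomes under that rule are these:

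- Section 2.3 (Outcome), primary: "The major result is rate of PU healing or ulcer epithelialization tissue".
- Section 2.3, secondary: "The secondary result is the changes in the area of ulcer in cm and cost-effectiveness".
- Section 3 (Result), Table 1, has a P value column and six rows. Two are naturally categorical: "Rate of pressure ulcer healing" and complications. Four are numeric: "Changes in the area of ulcer", medical cost, frequency of dressing and length of hospitalization.

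On size, section 2 (Methods) states that "each group includes 48 participants", so 96 patients in total.

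**The concern.** The order of the two lists, joined by the word respectively, fixes the pairing: the first test (t) goes with the first variable type (categorical), and the second test (chi-square) with the second (continuous). That is backwards. The t test compares means of a numeric variable. Pearson's chi-square compares category frequencies and takes no account of the order or spacing of the values.

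Applied to a measurement such as change in ulcer area, chi-square treats every distinct number as its own unordered category, so a systematic shift between the groups is largely or wholly invisible to it. At stake are the P values for the four numeric rows, including area change, which section 2.3 names as a secondary outcome, and cost, which feeds the other secondary outcome. An analyst who follows the text loses those comparisons. One who runs the usual tests departs from the published rule.

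**Working it through.** The article gives no power, effect size or standard deviation, so there is no stated figure to reproduce. The check asks what the sentence does at the stated group size.

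**Inputs from the document.** n = 48 per group, N = 96 (section 2). Significance level 0.05 (section 2.4). Sidedness is not stated; two-sided is assumed.

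**Assumptions.** Normally distributed outcomes with equal SD; true differences of 0.5 SD and 1 SD; for the case with ties, values rounded to a grid of 0.2 SD; for binary outcomes, common event rates of 0.05 to 0.7.

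**Step 1. Chi-square on a continuous outcome, no ties.** If all 96 values differ, the table has 96 rows and 2 columns, and each row holds one patient. With equal groups, each expected count is 1 × 48/96 = 0.5. Each row contributes

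(1 − 0.5)²/0.5 + (0 − 0.5)²/0.5 = 0.5 + 0.5 = 1.

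The sum over 96 rows is 96, on (96 − 1)(2 − 1) = 95 degrees of freedom, giving P = 0.452. Which values fall in which group does not enter the calculation, so the result is the same for any treatment effect and power is zero.

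**Step 2. Chi-square on a continuous outcome, with ties.** Proportion of 2000 simulated trials with P < 0.05 (t test on the unrounded values, chi-square on the rounded values):

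| True difference | t test | Chi-square, values rounded to 0.2 SD |
|---|---|---|
| 0 | 0.048 | 0.0215 |
| 0.5 SD | 0.671 | 0.076 |
| 1 SD | 0.998 | 0.491 |
| 2 SD | 1.000 | 0.999 |

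The normal-approximation formula for the t test, power = Φ(d√(n/2) − 1.96), agrees with the simulation. For d = 0.5: 0.5 × √24 = 2.449, and Φ(0.489) = 0.69. For d = 1: 4.899 − 1.96 = 2.939, and Φ(2.939) = 0.998.

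**Step 3. t test on a yes/no outcome.** With values coded 0/1, the pooled t statistic is a function of the Pearson chi-square: t² = χ²(N − 2)/(N − χ²). At the chi-square cut-off of 3.841, t² = 3.841 × 94/(96 − 3.841) = 3.918, against the two-sided 5% cut-off for t² on 94 degrees of freedom of 1.9855² = 3.942. The two tests therefore reject at almost the same point. Exact type I error, by enumerating all pairs of event counts at 48 per group:

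| Common event rate | t test | Chi-square |
|---|---|---|
| 0.05 | 0.043 | 0.052 |
| 0.1 | 0.049 | 0.059 |
| 0.3 | 0.048 | 0.052 |
| 0.5 | 0.052 | 0.052 |
| 0.7 | 0.048 | 0.052 |

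So the reversal does real damage to numeric outcomes and very little to binary ones.

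**The case against.** The strongest reply is that this is a slip of word order in an article whose English is irregular throughout, and that nobody will run a 96-row chi-square on ulcer area. That is probably right, and it lowers the chance of actual harm. It does not make the sentence correct. This is not detail left to a fuller document but a rule stated in current text; an analysis plan with the right pairing would contradict the article, and the article would still need correcting.

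Four stronger readings are tempting, and the document does not support them.

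- A reader might infer that no outcome in Table 1 can be validly analysed. If healing and complications are yes/no, step 3 shows that the t test is approximately valid for them. The article does not define healing closely enough to be sure that it is binary, but it also names no outcome with three or more unordered categories, where a t test would be meaningless.
- A reader might infer that power is zero for every numeric row. That holds only if all 96 values differ. The article does not say how finely outcomes are recorded. Dressing frequency is a count and will have ties, as would length of stay in whole days. With ties the loss is severe but not total, and it depends on the effect.
- A reader might infer that the primary outcome is lost. Read as a healed/not healed proportion, it is barely affected.
- A reader might add that medians are mentioned without a rank test. Section 2.4 offers the median only as one example of a summary and ties it to no outcome. A rank test, or an exact test for small counts, is detail that a condensed article may leave to the analysis plan.

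**Conclusion.** The point holds in limited form: section 2.4 states the test assignment the wrong way round, and no other part of the article corrects it. The consequence is confined to the numeric rows of Table 1. For these, the rule as written gives a fixed P of 0.45 when all values are distinct. Under the assumed rounding to 0.2 SD, it cuts power from about 0.67 to 0.08 at a 0.5 SD difference, and from 0.998 to 0.49 at 1 SD. The type I error falls to about 0.02, so the error runs towards missed differences rather than false ones. For yes/no outcomes, type I error stays between 0.043 and 0.052 and the harm is small. The power figures rest on the assumed effect sizes, normality, grid width and two-sided testing. The reversal itself rests only on the wording, and the no-ties result only on the 48 per group stated in section 2.

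**What to change.** Swap the two variable types in the sentence in section 2.4, so that independent t tests are assigned to continuous variables and chi-square tests to categorical variables. Nothing further is needed to resolve this point. With the pairing restored, power for a continuous outcome at 48 per group is about 0.69 by formula (0.67 simulated) at an assumed 0.5 SD difference and 0.998 at 1 SD. The chi-square type I error for a binary outcome is 0.052 to 0.059 over the assumed event rates.

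The cost is one corrected sentence. Patients, procedures, data collection and sample size are unaffected. The correction should be recorded before the data are analysed, so that running the standard tests is not an undocumented departure from the published plan. If a separate analysis plan exists, its wording should be checked against the corrected sentence.

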## Result

3

Table 1 will show the comparison of clinical outcomes between 2 groups.

**Table 1 T1:** Comparison of clinical outcomes between 2 groups.

	Polyurethane foam dressing group (n = 48)	Hydrocolloid dressing group (n = 48)	*P* value
Rate of pressure ulcer healing			
Changes in the area of ulcer			
Medical cost			
Frequency of dressing			
Length of hospitalization			
Complications			

## Discussion

4

PUs (also known as bed sores, decubitus ulcers, and pressure sores) refers to the wounds to the underlying tissue and skin resulted from rubbing or pressure.^[14,15]^ They generally generate in the bony parts of the body or in places that bear pressure or weight, for instance, the buttocks, hips, elbows, and heels. People who stay in bed for a long time or are unable to move may suffer from PUs, especially the elderly and other vulnerable groups of patients.^[16,17]^ PUs have a significant negative influence on the patients, and they continues to lead to the cost burden on the hospital providers, driven mainly by resources devoted to treating the complications.^[18,19]^ The PUs patients may have longer hospital stays, higher mortality rates during hospitalization, and higher rate of readmission. The special dressings can utilize as the barrier to bacteria, decreasing the pain in the process of healing, absorbing the excess wound fluid, and then generate the suitable conditions for healing and scarring. Several types of dressings have been used in treating PUs and the optimal one remains controversial.

## Conclusion

5

This study can develop an evidence-based protocol to identify optimal dressings for patients with PUs.

## Abbreviations

Abbreviation: PU = pressure ulcer.
